8.1 Safety Outcome Analysis Plan

The primary safety outcome is the frequency and proportion of adverse events. Adverse event data will be summarized by the number of cases and proportion in each group, with 95% exact binomial confidence intervals. Between-group comparisons will be made using Pearson’s chi-square test (Fisher’s exact test if needed).

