3.3 Allocation

• Allocation Ratio: 1:1

• Method: Stratified block randomization

• Adjustment Factors: Mode of delivery (vaginal delivery, cesarean section), severity of anemia (Hb < 8 g/dL, Hb ≥ 8 g/dL).

• Rationale for Adjustment Factors: To account for differences in blood loss during delivery and the effect of anemia treatment based on anemia severity.

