2.4 Significance Level and Confidence Interval

Unless otherwise specified, the significance level for hypothesis testing will be two-sided at 5%, and 95% confidence intervals will be calculated.

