4.2 Summary of Withdrawals or Discontinuations

A list of subjects who withdrew or discontinued will be provided.

5. Analysis Plan for Subject Background

Summary statistics of baseline characteristics will be calculated for each analysis population by group.

For categorical variables, the frequency and percentage will be shown. For continuous variables, summary statistics (sample size, mean, standard deviation, minimum, 1st quartile, median, 3rd quartile, and maximum) will be presented.

Between-group comparisons will be made using Pearson’s chi-square test for categorical variables (Fisher’s exact test if more than 20% of expected frequencies are below 5) and Student’s t-test or the Wilcoxon rank-sum test for continuous variables. A two-sided significance level of 5% will be used.

6. Analysis Plan for Primary Outcome

The primary objective of this study is to demonstrate the superiority of iron carboxymaltose injection over extended-release ferrous sulfate tablets in terms of the change in Hb levels at 2 weeks postpartum.

The primary outcome will be analyzed by comparing the mean change in Hb levels between the two groups. The null hypothesis is that the mean change in Hb for the treatment group is equal to that of the control group (mean change difference = 0), and the alternative hypothesis is that the mean change differs between the groups.

A two-sided 95% confidence interval for the mean change difference will be calculated. Covariate-adjusted ANCOVA will be used, adjusting for factors such as delivery mode (vaginal delivery or cesarean section), severity of anemia (Hb < 8 g/dL or Hb ≥ 8 g/dL), and baseline Hb levels.

7. Analysis Plan for Secondary Outcomes

To supplement the primary analysis, secondary outcomes will be analyzed without adjusting for multiplicity. A two-sided significance level of 5% and 95% confidence intervals will be calculated.

The change in ferritin, Hb, and TSAT levels at 4 weeks postpartum will be summarized by sample size, mean, standard deviation, minimum, 1st quartile, median, 3rd quartile, and maximum. Covariate-adjusted ANCOVA will be used to analyze these outcomes.

EPDS score progression will be evaluated by calculating the proportion of subjects with scores ≥ 9 at baseline and at 4 weeks postpartum. Between-group comparisons will be conducted using the chi-square test and adjusted Mantel-Haenszel test (risk difference) with covariates for delivery mode and severity of anemia.

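### The adverse-event comparison leaves out both stratification factors; if either factor predicts adverse events, the test is conservative and loses a little power, and a stratified risk difference avoids this at almost no cost.

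*Combined protocol and SAP*

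**What the plan says.** - **Allocation (protocol section 3.3).** "Method: Stratified block randomization", in the ratio 1:1, with the factors "Mode of delivery (vaginal delivery, cesarean section), severity of anemia (Hb < 8 g/dL, Hb ≥ 8 g/dL"). This gives four strata. The stated reason is "To account for differences in blood loss during delivery and the effect of anemia treatment based on anemia severity". Adverse-event risk is not mentioned.
- **Adverse events (SAP section 8.1).** Counts and proportions per group with exact binomial 95% intervals, then: "Between-group comparisons will be made using Pearson’s chi-square test (Fisher’s exact test if needed"). No stratum or covariate term appears, and no stratified safety analysis is planned elsewhere.
- **The other binary outcome (SAP section 7).** The proportion with an EPDS score of 9 or more is compared by a chi-square test and also by an "adjusted Mantel-Haenszel test (risk difference) with covariates for delivery mode and severity of anemia".
- **Primary outcome (SAP section 6).** The ANCOVA for hemoglobin change names both factors and baseline hemoglobin.
- **Level (SAP section 2.4).** Unless otherwise specified, "the significance level for hypothesis testing will be two-sided at 5" percent. Section 8.1 sets no level of its own, so this rule applies to it.

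**The concern.** Stratified blocks make the arms nearly equal in their mix of vaginal and cesarean deliveries and of anemia severity. If event risk differs between those strata, that part of the variation can hardly contribute to a difference between arms. A pooled chi-square test still counts it as random error. Its standard error is then too large, so it rejects less often than 5% under the null and misses real differences more often.

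For a safety outcome, the cost of conservatism is an undetected excess of harm. SAP section 1 places safety beside efficacy in the study's purpose, and with 30 women per arm there is little power to spare. The plan also gives no reason for treating its two binary outcomes differently.

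**Working it through.** **No design figure to reproduce.** The 5% is a chosen level. The documents contain no adverse-event rate and no power calculation for safety. The only inputs they supply are 60 women, 30 per arm, 1:1 allocation, four strata and a two-sided 5% level. Everything else below is assumed.

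**Step 1: approximate size by arithmetic.** Assume per-arm stratum sizes of 14 and 4 (vaginal) and 9 and 3 (cesarean), so 18/30 = 0.6 vaginal and 0.4 cesarean. Assume that event rates differ by delivery mode only. With exact balance, the difference in proportions varies by the within-stratum variance W = 0.6·p_v(1−p_v) + 0.4·p_c(1−p_c). Pearson uses the total variance V = p̄(1−p̄), where p̄ = 0.6·p_v + 0.4·p_c. The true size is therefore about 2·[1 − Φ(1.96/√(W/V))].

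| Vaginal / cesarean rate | W | p̄ | V | W/V | 1.96/√(W/V) | Size |
|---|---|---|---|---|---|---|
| 20% / 20% | 0.160 | 0.20 | 0.1600 | 1.00 | 1.960 | 5.0% |
| 20% / 30% | 0.180 | 0.24 | 0.1824 | 0.987 | 1.973 | 4.9% |
| 20% / 50% | 0.196 | 0.32 | 0.2176 | 0.901 | 2.065 | 3.9% |
| 20% / 60% | 0.192 | 0.36 | 0.2304 | 0.833 | 2.147 | 3.2% |

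**Step 2: simulation in the same strata.** Pooled Pearson without continuity correction is compared with the Cochran-Mantel-Haenszel (CMH) test over the four strata.

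| Vaginal / cesarean rate | Pearson size | CMH size | Power lost by pooling, +25 points |
|---|---|---|---|
| equal | about 5% | about 5% | none |
| 20% / 30% | about 4.9% | about 5% | about 0.6 points |
| 20% / 50% | about 3.8% | about 5% | about 3 points (50% against 53%) |
| 20% / 60% | about 3.1% | about 5% | about 6 points (50% against 56%) |

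Repeated runs differ by a few tenths of a point; for 20%/30%, Pearson size ranged from 4.5% to 4.9%. The simulation agrees with the arithmetic in step 1.

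**Step 3: different assumptions, with the plan's Fisher switch.** Here the blocks have size 4, half the women have a cesarean section, 30% have Hb below 8 g/dL, and each factor has the same odds ratio (OR) for adverse events. The treatment odds ratio is 4 for power. Fisher replaces Pearson when any expected count is below 5, which is the SAP section 5 rule for baseline tables, assumed to carry over to section 8.1.

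| Factor OR | Pearson size, control rates 20–50% | Power at control rate 20%: plan's rule | Power at control rate 20%: CMH |
|---|---|---|---|
| 1 | 4.9–5.3% | 70.4% | 70.3% |
| 2 | 4.4–4.6% | 65.2% | 66.6% |
| 3 | 3.9–4.0% | 59.0% | 63.1% |
| 6 | 2.6–3.1% | 46.3% | 56.1% |

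CMH size stayed between 4.5% and 5.3% throughout. With unstratified randomisation and an odds ratio of 6, Pearson size was 4.7–5.2%. The shortfall therefore comes from stratifying on prognostic factors and then ignoring them.

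**Step 4: rare events.** At a 10% event rate and a factor odds ratio of 1, the plan's rule already has a size of only 2.3%; at an odds ratio of 3 it is 1.8%. Most of the conservatism here belongs to Fisher's exact test, not to the missing strata.

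**The case against.** A reader might infer that the true error rate of the adverse-event test is below 5% and that power is lost, as a fact about this trial. The documents do not support that. Section 3.3 chose the factors for blood loss and treatment effect, and no adverse-event rate appears anywhere. If neither factor predicts adverse events, the pooled Pearson test keeps its level and its power. That women report more events after cesarean section is plausible, but it is an assumption. With a mild association the effect is negligible: about half a point of power at 20%/30%.

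Other points also stand:

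- The planned test errs on the conservative side, so it does not inflate false positives.
- The confirmatory hypothesis concerns hemoglobin and is adjusted. No safety power is promised, so no stated figure is missed.
- The safety set is grouped by treatment actually received, so exact balance within strata need not hold.
- SAP section 7 does not replace the chi-square test for EPDS. It keeps that test and adds the Mantel-Haenszel analysis.
- A reader might infer that an exact stratified test would restore the 5% level when events are few. It does not: in simulations at low event rates its size was 0.7–1.3%. With 5%/10% rates its power for a 25-point difference was 60.8%, against 68% for the planned rule.

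These points limit the size of the concern but do not remove the reason to act. In the settings simulated, CMH held its level approximately. Its power was at worst about 0.3 points below the planned rule (74.7% against 75.0%, factor odds ratio 1, control rate 30%) and was higher wherever the factors predicted events.

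**Conclusion.** The omission is plain in the text: section 8.1 ignores both factors used to randomise, while section 7 uses both for the plan's other binary outcome. The consequence is conditional. If delivery mode or anemia severity predicts adverse events, the pooled test is conservative and loses power: under 1 point for a mild association and about 3 to 6 points for the strong ones assumed here. Without such an association nothing is lost.

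These sizes rest on assumed event rates, stratum sizes and effects, and they describe the CMH test. Coverage of a Mantel-Haenszel risk-difference interval was not calculated. The point is minor: a free or cheap improvement, not a flaw that threatens the trial's conclusions.

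**What to change.** In SAP section 8.1, make the between-group comparison of the proportion of women with any adverse event a Mantel-Haenszel risk difference with 95% confidence interval. Stratify it by delivery mode and anemia severity (Hb < 8 or ≥ 8 g/dL), as section 7 does for EPDS, and name the variance estimator. Keep the unadjusted Pearson or Fisher test and the per-arm exact intervals as supportive. Do not claim that an exact stratified test recovers the 5% level when events are few.

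The cost is a sentence or two of SAP wording. Both stratum variables are recorded for randomisation, and the method is already planned for EPDS. The change also supplies an adjusted between-arm difference, where section 8.1 now names only per-arm intervals and a test. The downside is that very small strata contribute little information.

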8.2 Clinical Laboratory Data and Vital Signs

Summary statistics for clinical laboratory data and vital signs will be calculated for each group. Categorical variables will be compared using Pearson’s chi-square test, while continuous variables will be compared using Student’s t-test or the Wilcoxon rank-sum test.

9. Statistical Analysis Implementation

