5.6 Laboratory Tests

Blood tests will be conducted twice, requiring 10 ml of blood each time.

6. Target Number of Subjects and Planned Period

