1.2 Primary Outcome Measure

Efficacy:

Change in Hb levels at 2 weeks after administration (2 weeks postpartum).

Calculation: Change = Value at 2 weeks after administration − Value at baseline (registration and start of treatment).

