2.3 Data Handling

The analysis will target fixed data after the follow-up period ends.

For values below the detection limit, half of the detection limit value will be substituted.

Definitions for change and rate of change:

Change: Measurement after intervention − Baseline measurement.

Rate of Change: (Change / Baseline measurement) × 100 (%).

If necessary, variable transformations such as square root or logarithmic transformations will be performed.

Missing data will not be considered in the analysis or secondary analysis, but sensitivity analysis (e.g., multiple imputation) will be conducted as needed to assess the stability of the results.

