3.2 Correspondence with Statistical Analysis Items

Efficacy evaluations will primarily be based on the FAS. The PPS analysis will be conducted as a reference. Safety evaluations will be based on the safety analysis set.

4. Plan for Breakdown and Exposure Analysis

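### SAP 8.2 compares continuous laboratory and vital-sign variables without a baseline covariate, leaves the test open, and does not exclude the efficacy analytes (minor)

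*Combined protocol and SAP*

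**What the plan says.** SAP 8.2, under the safety analysis plan, has two parts. The first is descriptive: "Summary statistics for clinical laboratory data and vital signs will be calculated for each group". The second is inferential: categorical variables go to a chi-square test, and "continuous variables will be compared using Student’s t-test or the Wilcoxon rank-sum test". The section lists no analytes or time points, does not say whether follow-up values or changes are compared, and names no covariate.

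Three other places bear on it:

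- SAP 6, for the primary outcome (change in Hb at 2 weeks): "Covariate-adjusted ANCOVA will be used, adjusting for factors such as delivery mode". The covariate list ends with "severity of anemia (Hb < 8 g/dL or Hb ≥ 8 g/dL), and baseline Hb levels". SAP 7 also uses covariate-adjusted ANCOVA for ferritin, Hb and TSAT at 4 weeks, without listing the covariates.
- SAP 2.3 gives a general definition: "Change: Measurement after intervention − Baseline measurement". Section 8.2 does not refer to it.
- SAP 3.2 puts efficacy primarily on the FAS, and "Safety evaluations will be based on the safety analysis set". SAP 3.1.3 groups that set by treatment actually received.

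On what is measured, protocol 5.6 says only: "Blood tests will be conducted twice, requiring 10 ml of blood each time". Protocol 5.4 lists four vital signs without a schedule.

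**The concern.** The plan handles continuous measurements of the same kind in two ways and gives no reason. Hb, ferritin and TSAT get a covariate-adjusted model; every other continuous laboratory value and vital sign gets a two-sample test with no stated use of baseline. With 30 women per arm, an unadjusted comparison gives up precision whenever baseline and follow-up are more than weakly correlated, so a real shift in a safety variable is easier to miss.

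Two smaller matters follow from the same sentence. First, with no rule for choosing between the t-test and the Wilcoxon test, the choice can be made after seeing the data, in an open-label trial. Second, Hb, ferritin, serum iron and TIBC are blood measurements, and 8.2 covers clinical laboratory data without exclusions. A programmer could reasonably produce a second between-arm p-value for Hb, unadjusted and in the safety set, beside the ANCOVA result in the FAS. If the two disagree, the report has to explain a conflict that the plan could have prevented.

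**Working it through.** The plan gives no figure to reproduce: 8.2 states no number, and the supplied text gives no SD, effect size or correlation. The precision figures are therefore ranges over an assumed correlation ρ between baseline and follow-up.

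**Inputs from the documents:** 30 per arm (protocol 6.1); two-sided 5% level (SAP 2.4); no multiplicity adjustment (SAP 2.5).

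**1. Variance of the treatment effect.** Assume equal variances at baseline and follow-up, and take a t-test on follow-up values as 1. Then ANCOVA has 1 − ρ² and a t-test on change has 2(1 − ρ). ANCOVA relative to change is (1 − ρ²) / [2(1 − ρ)] = (1 + ρ)/2.

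| ρ (assumed) | ANCOVA vs raw values | ANCOVA vs change |
|---|---|---|
| 0.3 | 1 − 0.09 = 0.91 | 1.3/2 = 0.65 |
| 0.5 | 1 − 0.25 = 0.75 | 1.5/2 = 0.75 |
| 0.7 | 1 − 0.49 = 0.51 | 1.7/2 = 0.85 |

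Against raw values, the confidence interval narrows by 1 − √0.91 = 5%, 1 − √0.75 = 13% and 1 − √0.51 = 29%.

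**2. Power.** Take the difference that gives the raw-value t-test 80% power: (1.960 + 0.842) × √(2/30) = 0.723 SD. Multiplying the SD by √(1 − ρ²), ANCOVA power is 84%, 90% and 97.5% at ρ = 0.3, 0.5 and 0.7. A t-test on change has 66%, 80% and 95%. These are normal approximations.

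**3. Cost of the covariates.** Estimating q covariates inflates the variance by about 1 + q/(60 − q − 3). One covariate gives 1 + 1/56 = 1.018. Own baseline plus the two randomisation factors gives 1 + 3/54 = 1.056, if those factors explain nothing further. The ratios against raw values become 0.91 × 1.056 = 0.96, 0.75 × 1.056 = 0.79 and 0.51 × 1.056 = 0.54. At ρ = 0.2 the result is 0.96 × 1.056 = 1.01, so there is no gain over raw values for a weakly correlated variable.

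**4. Open choice of test.** In 100,000 simulated null trials per distribution at 30 per arm, a finding was counted if either test gave p < 0.05.

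| Distribution | t-test | Wilcoxon | Either |
|---|---|---|---|
| Normal | 4.9% | 4.8% | 5.8% |
| t, 3 df | 4.5% | 4.8% | 6.4% |
| Lognormal | 4.1% | 4.8% | 6.8% |

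**5. Possible conflict on Hb.** Assume a baseline SD of 0.8 g/dL, residual SD 0.9 g/dL, slope 0.4–0.6 and true difference 0.6–0.7 g/dL. In simulated trials, the ANCOVA and an unadjusted t-test (raw or change) then fall on opposite sides of p = 0.05 in roughly 8–18% of trials, depending on the setting. The difference in method alone produces this; no difference in population is needed.

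**The case against.** The strongest defence is that nothing here is invalid. Unadjusted tests are sound in a randomised comparison, the plan sets no power target for these variables, and SAP 8.1 makes adverse events the primary safety outcome. That stands: the point concerns efficiency and consistency.

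Three stronger readings are tempting, and the documents do not support them.

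- *That 8.2 plans a second test of the primary outcome.* The section never names Hb and sits under safety, while Hb, ferritin and TSAT are assigned to SAP 6 and 7. That the documents name no other analytes proves little, because protocol 5.6 has no analyte list. A second Hb test is a reading that is not excluded; it is not a stated plan.
- *That baseline is ignored.* Section 8.2 is silent, and SAP 2.3 defines change, so change scores may be intended. The accurate statement is that no use of baseline is specified. ANCOVA has the smaller variance on either reading once ρ is more than weak.
- *That the confirmatory type I error is inflated.* SAP 6 fixes the ANCOVA and SAP 3.2 places efficacy primarily on the FAS. Counting the ANCOVA, t-tests on both raw and change values, and a Wilcoxon test together gives about 9–10% under the null, but 8.2 does not plan that set of tests.

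Two further limits hold. The safety set may be almost the same as the FAS: they differ only through missing baseline Hb, major violations and as-treated grouping. A baseline is documented for Hb but not for every vital sign or other analyte, so ANCOVA cannot be prescribed for all variables.

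**Conclusion.** The point holds as a minor matter of precision and consistency. Section 8.2 specifies valid but less efficient comparisons and leaves open the test, the time point and the quantity compared.

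The gain from baseline adjustment depends on a correlation that the documents do not give. Against raw values it ranges from small at ρ = 0.3 to about half the variance at ρ = 0.7. Against change scores it is 35% of the variance at ρ = 0.3, falling to 15% at ρ = 0.7. The covariate cost of about 6% comes off these gains. The open choice of test adds at most about two percentage points to the false-positive rate per variable.

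The overlap with Hb, ferritin and TSAT is an ambiguity worth closing because a conflicting p-value would be awkward to report. The primary analysis and its 5% level are unaffected.

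**What to change.** In SAP 8.2:

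(a) For continuous variables with a recorded baseline, replace the t-test/Wilcoxon choice by ANCOVA on the follow-up value at a stated time point. Use that variable's own baseline and the two randomisation factors (delivery mode and anemia severity) as covariates, and log-transform skewed variables, as SAP 2.3 allows. Report the adjusted difference with its 95% CI. Summarise variables without a baseline descriptively.

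(b) State that Hb, ferritin, serum iron, TIBC and TSAT are compared between arms only under SAP 6 and 7, where those sections plan a comparison, and are summarised descriptively in 8.2.

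Cost: a few sentences of SAP text and slightly more programming, with no new data or patients. The downside is a model assumption for skewed variables and little or no gain for variables whose baseline predicts follow-up weakly.

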9.2 Statistical Software

Statistical analyses will be performed using SAS 9.4 or later (Windows version, 32-bit or 64-bit).
